## Abstract

**Introduction:**

Psoriasis is a chronic inflammatory skin disease that significantly impacts patients’ quality of life. Although biological therapies are effective, they are associated with high costs and potential side effects, necessitating strategies for dose reduction. Pharmacological conditioning, using placebo mechanisms through associative learning, presents a promising approach to maintain therapeutic efficacy with lower doses of medication.

**Methods and analysis:**

The single-centre, randomised controlled trial aims to investigate pharmacological conditioning with secukinumab in patients with moderate-to-severe psoriasis (N=168). Participants will be randomly allocated to a treatment-as-usual group or one of two experimental groups receiving partial or continuous reinforcement schedules with reduced secukinumab doses combined with a distinctive gustatory stimulus. Primary outcomes include changes in itch intensity, skin-related quality of life and objective disease severity. Secondary outcomes encompass psychological variables, side effects and biological markers. Results may contribute to optimised long-term psoriasis management, reducing medication burden while maintaining treatment efficacy.

**Ethics and dissemination:**

The study protocol was approved by the ethics committee of the University Hospital Essen (19–8636 BO) on 20 November 2023. Written informed consent will be obtained from all participants. Participant confidentiality will be ensured through pseudonymised data handling and secure storage. The results will be disseminated through peer-reviewed publications.

**Trial registration number:**

DRKS00034977.

STRENGTHS AND LIMITATIONS OF THIS STUDYThe longitudinal design (10 assessments) enables modelling of dynamic symptom trajectories in addition to pre–post change.The comparison of two dose-reduction regimens against each other and against standard dosing informs individualised treatment strategies.The merging of the two conditioning groups allows equalising sample sizes for the non-inferiority test, whereas statistical power may be limited for arm-specific comparisons with treatment-as-usual.With no low-dose, non-conditioned controls, pharmacological low-dose effects cannot be disentangled from conditioning effects.

## Introduction

 Psoriasis is a chronic inflammatory skin disease affecting approximately 2–3% of the global population and is associated with burdening psychosocial comorbidities including depression, anxiety disorders and suicidal ideation.^1^,^3^ Psoriasis is a lifelong relapsing and remitting condition that significantly impairs patients’ quality of life, as it is often accompanied by physical discomfort, impaired emotional functioning, a negative body- and self-image and limitations in daily activities.^4^

Over the last decade, treatment options for psoriasis have massively expanded. Advanced systemic therapies now include the latest generation of biologics, specifically targeting pro-inflammatory cytokines identified as pivotal in pathophysiology of psoriasis such as interleukin (IL)-17 and IL-23. These modern cytokine blockers have demonstrated high efficacy in alleviating symptoms in patients with moderate-to-severe psoriasis.^5^ However, biologics impose a significant economic burden and carry potential side effects, which can negatively affect patients’ adherence to treatments.^5^,^10^ As a result, dosage reduction strategies were proposed as a possibility to optimise treatment efficacy while minimising risks and healthcare costs.^11^

Although reviews have summarised existing clinical studies on dose tapering of biologics in psoriasis,^11 12^ most studies investigated stepwise dose reduction based on clinical stability criteria, without reference to psychological mechanisms or behavioural frameworks. However, recent research suggests that such mechanisms may offer a promising avenue for enhancing symptom relief beyond the pharmacological action of the drug itself.^13^ Placebo effects, traditionally considered a confounding factor in clinical trials, may in fact be intentionally used for therapeutic purposes.

A large body of evidence indicates that treatment expectations, as a core psychological mediator of placebo effects, significantly influence both the efficacy and tolerability of pharmacological treatments across a wide range of clinical conditions.^14^,^20^ This is particularly relevant in dermatology, where clinical studies have demonstrated that skin diseases and allergic reactions can be modulated through various methods of inducing placebo effects, such as enhancing positive treatment expectations or using implicit learning mechanisms like pharmacological conditioning.^16 20 21^ Given that placebo effects can induce measurable symptom relief independent of active pharmacological agents, their systematic integration into psoriasis treatment could serve as a complementary strategy to help sustain symptom control despite lower biological dosages. This would optimise treatment outcomes while reducing costs and potential side effects.

One particularly promising target for such an approach in psoriasis patients is itch, which affects approximately 85% of patients and represents a core symptom of psoriasis.^22^ Beyond its physical manifestation, itch significantly impacts patients’ quality of life, contributing to emotional distress, impaired daily functioning and reduced overall well-being.^23^ Notably, itch is highly susceptible to psychological influences,^16 20^ as cognitive and emotional factors can modulate its perception and intensity. A key mechanism underlying this susceptibility is the skin-brain axis, a bidirectional communication system linking psychological states to immune and inflammatory processes in the skin.^24 25^ This makes itch a particularly promising target for placebo-based interventions and further supports the rationale for harnessing placebo effects in psoriasis treatment. Accordingly, placebo effects on itch are routinely observed in the treatment of various dermatological conditions, including psoriasis.^2021 26^,^28^ Clinical and experimental studies have demonstrated that these placebo effects are mediated by treatment expectations and implicit learning processes.^16 20^ While these findings highlight the general susceptibility of itch to placebo mechanisms, most work has focused on acute placebo effects induced by verbal suggestions, which were shown to induce conscious positive treatment expectations,^29^,^31^ but show limited efficacy in sustaining long-term symptom control, which is particularly relevant for chronic conditions such as psoriasis.^32^ Preliminary evidence from a recent randomised controlled trial conducted by our research group supports the notion that verbal suggestions alone may not be sufficient to generate sustained placebo effects in chronic inflammatory conditions such as psoriasis.^33^ In this trial (N=120), patients with moderate-to-severe psoriasis received the IL-17A antagonist secukinumab and were assigned to one of three groups: standard treatment (300 mg), a dose-reduction group (75 mg) and an experimental group receiving the same reduced dose along with verbal suggestions aimed at enhancing positive treatment expectations. While all groups showed symptom improvement over time, verbal suggestions did not significantly reduce subjective itch, quality of life or objective symptom scores compared with dose reduction alone, suggesting limited efficacy of conscious expectation modulation.

Given these limitations, approaches that use implicit learning processes—such as pharmacological conditioning—may offer a more effective means of sustaining symptom relief in chronic diseases like psoriasis. Unlike verbal suggestions, which primarily induce conscious expectations, pharmacological conditioning engages implicit learning processes, in which repeated pairing of an active drug with a neutral stimulus (eg, the appearance or intake of a medication) leads to the conditioned stimulus alone eliciting a physiological response similar to that of the drug.^13 34^ This approach has shown potential in dermatology, as demonstrated by evidence from experimental itch research suggesting that conditioning-based placebo effects are more robust and longer-lasting than those induced by verbal suggestions alone, especially when both mechanisms are combined.^35^,^37^

A proof-of-concept study by Ader and colleagues^38^ performed in patients with mild-to-moderate psoriasis provides preliminary clinical evidence for the efficacy of pharmacological conditioning in psoriasis treatment. In a partial reinforcement schedule, active corticosteroids were intermittently replaced with a placebo after an acquisition phase with full dose medication administration. Results indicated a greater amelioration of symptoms and less relapse for partial reinforcement when compared with a continuous reinforcement schedule with the same cumulative amount of the drug.^38^ To date, this study remains the only one which investigated pharmacological conditioning as a dose-reduction strategy in the treatment of psoriasis. Nevertheless, the study highlights the potential of personalised reinforcement schedules as an adjunct to standard psoriasis treatment.

Building on the promising findings of Ader and colleagues, our present study aims to expand on this preliminary evidence by investigating the effects of pharmacological conditioning as a dose-reduction strategy in systemic psoriasis treatment with the IL-17 inhibitor secukinumab. To further optimise associative learning and enhance response durability, the study intentionally selects the conditioned stimulus based on general principles derived from experimental evidence. Specifically, data suggest that the success of pharmacological conditioning depends critically on the characteristics of the conditioned stimulus. To maximise learning efficiency, the conditioned stimulus should be perceptually distinct and highly associable with the pharmacological effect.^13^ Prior research on preparedness has shown that certain sensory stimuli—particularly gustatory cues—are more readily linked to immune-related responses, making them particularly well-suited for conditioning paradigms involving psoriasis.^39^ Additionally, the salience and uniqueness of a drug, including its appearance, taste and mode of administration, have been found to influence the strength and persistence of conditioned responses.^40 41^ To systematically address these factors, our study employs a well-established green-coloured, novel-tasting drink (strawberry milk aromatised with lavender oil and dyed with green food dye) as described previously as a conditioned stimulus, designed to optimise associative learning processes and enhance response durability.^42^

By investigating pharmacological conditioning as a dose-reduction strategy in the systemic treatment of patients with moderate-to-severe psoriasis, this approach may offer a novel strategy to improve long-term disease management while minimising medication burden.

## Methods

### Trial design

To evaluate the efficacy of pharmacological conditioning as a dose-reduction strategy for patients with moderate-to-severe psoriasis, a single-centre, non-inferiority study with a randomised factorial design will be conducted at the Department of Dermatology, University Hospital Essen, Germany.

In order to assess non-inferiority of pharmacological conditioning compared with standard treatment, eligible patients will be randomly assigned in a 2:1:1 allocation ratio to one of three study arms: treatment-as-usual (TAU), partial reinforcement and continuous reinforcement, respectively. Patients in the TAU group will receive standard pharmacological treatment with full doses of the monoclonal antibody secukinumab, serving as the active control group. Patients in the partial reinforcement group will receive a reduced dose of secukinumab or a placebo at alternating visits, while those in the continuous reinforcement group will receive reduced doses of secukinumab throughout all visits. To disentangle potential dose effects from conditioning effects, the continuous reinforcement group serves as a dose-control group with identical cumulative dosage to the partial reinforcement group. This enables the evaluation of whether partial reinforcement schedules elicit stronger clinical effects than continuous reinforcement, despite equal drug exposure. In both reinforcement groups, a novel-tasting beverage will be administered in combination with the medication or placebo to elicit pharmacological conditioning. For an overview of the dosing schedule, see figure 1. The study was preregistered on 18 October 2024 at the German Clinical Trials Register (DRKS00034977) prior to the first recruitment on 13 December 2024 and is conducted as part of the Collaborative Research Center 289, which investigates the impact of patient expectations on the efficacy of medical treatments (https://treatment-expectation.de/en/). Recruitment is planned to continue until 30 June 2027. This study protocol adheres to the SPIRIT 2025 statement (Standard Protocol Items: Recommendations for Interventional Trials). The completed SPIRIT checklist is provided as online supplementary table 2.^43^

**Figure 1 F1:**
[figure not shown]
Dosing schedule at a glance. TAU, treatment-as-usual.

### Inclusion criteria

Patients eligible for the trial must meet the following criteria: a minimum age of 18 years, an indication for the initiation of a systemic biological therapy according to the German S3-guideline on psoriasis,^44^ a Psoriasis Area and Severity Index (PASI) score >10. All sexes are eligible for trial participation.

### Exclusion criteria

Patients are not eligible if they meet any of the following criteria: pregnancy, lactation, forms of psoriasis other than chronic plaque (eg, pustular, erythrodermic, guttate or drug-induced) psoriasis, insufficient comprehension and communication skills in the German language, inability to provide informed consent, contraindications to biological therapy with secukinumab, medical or psychiatric conditions that contraindicate therapy with secukinumab or participation in the study, ongoing use of systemic antipsoriatic treatments, as well as prior treatment with secukinumab.

### Study schedule

Patients will attend a total of 10 visits over 20 weeks, beginning with an eligibility screening prior to a baseline assessment (visit 0), followed by a 16-week treatment phase (visits 1–8) and a follow-up assessment at week 20 (visit 9). All study visits will take place in the clinical study centre of the Department of Dermatology, University Hospital Essen, Germany, and will be conducted by the study physician, research assistants and medical student assistants.

#### Recruitment and enrolment of patients

Patients will be recruited from the outpatient department and from the inpatient wards of the Department of Dermatology, Venereology and Allergology at the University Hospital Essen, Germany. Recruitment will be conducted directly by the treating physician, who will inform patients with moderate-to-severe psoriasis about the option to participate in a study evaluating the influence of psychological factors on the effectiveness of systemic therapy with the IL-17 inhibitor secukinumab on subjective and objective outcomes. Additionally, informational flyers about the study for referring dermatologists will be included in the patients’ discharge letters.

Interested patients will be invited to a clinical visit (visit 0) at the study outpatient clinic, where they will be asked to provide written informed consent for participation by the treating study physician. Patients will be informed that they will be randomly assigned to one of three groups testing different dosing protocols for secukinumab, with some groups receiving lower doses than the standard regimen.

Additionally, patients will be informed that, depending on group assignment, they will receive a novel-tasting beverage alongside their injections at each visit. The patient information further includes a timeline indicating when psychological variables and biological samples will be collected. It will be emphasised that group allocation will be disclosed at the end of the study and that all patients will have access to standardised treatment with secukinumab or another therapeutic option after the study.

Patients will be fully informed about potential side effects, their right to withdraw their consent for the study at any time and the confidentiality of their data. On enrolment, each participant will be assigned a unique pseudonym through the ALIIAS software.^45^ The pseudonym will be linked to the web-based survey platform LimeSurvey,^46^ which will be used to collect the survey data for the study.

#### Dosing schedule and administration

Patients in the TAU group (n=84) will receive the standard dosing regimen of 300 mg of secukinumab as weekly injections for 5 weeks (weeks 0–4), followed by 3 monthly injections in weeks 8, 12 and 16. The injections will be administered by the research assistant to ensure that the study physician remains blinded to group allocation. Patients in both reinforcement groups will initially receive weekly injections of 300 mg of secukinumab during an acquisition phase (weeks 0–1). After the acquisition phase, patients in the partial reinforcement group will receive alternating weekly injections of 150 mg of secukinumab or a placebo (ie, sodium chloride) for 3 weeks (weeks 2–4) followed by monthly injections in weeks 8, 12 and 16. Injections for the patients in the continuous reinforcement group will be administered in the same weekly and monthly schedule as in the other experimental group but will consist of a continuous dose of 75 mg of secukinumab. Both reinforcement groups will receive the same total amount of medication to ensure that any observed effects will be attributable to the pharmacological conditioning, rather than differences in the total doses of the medication in the TAU and partial reinforcement group.

Additionally, at each visit, patients in both reinforcement groups will be given a novel-tasting gustatory stimulus (ie, 100 mL of fruit milk dyed with green food colouring and infused with lavender oil) right before medication or placebo administration. The research assistant will conduct the administration of the beverage, accompanied by standardised information about its potential benefits via a medical educational video, which was developed in collaboration with the Collaborative Research Center’s (CRC) patient advisory board.

#### Baseline assessment (visit 0)

Prior to the start of the treatment phase, patients will complete a baseline assessment during visit 0. After providing written informed consent, they will first complete a battery of psychological self-report questionnaires. This will be followed by a clinical consultation with the study physician, during which objective symptom severity will be assessed using the PASI. In addition, blood samples will be collected to monitor physiological parameters and for subsequent cytokine analysis. Saliva samples will also be collected for cortisol level analysis during this visit. Optionally, a skin biopsy will be obtained prior to the administration of the first dose of medication (ie, before visit 1).

#### Treatment phase and follow-up assessment

##### Visit 1

Similar to the procedure at visit 0, patients will start by completing psychological self-report questionnaires, followed by the clinical assessment conducted by the study physician. In contrast to visit 0, no biological samples will be collected. For patients assigned to one of the reinforcement groups, a 2-minute-35-second long medical educational video will be shown. The video will refer to a novel tasting green beverage, which, when taken in conjunction with the medication, can increase its effect via conditioning processes. Patients will be informed that they will receive the beverage immediately prior to their medication at every visit throughout the treatment phase. A literal transcription of the original German script as well as an English translation is provided as supplementary material (online supplemental text 1 and 2). The administration of the green beverage prior to the medication administration will be performed as the final step of each visit during the treatment phase.

##### Visit 2–visit 8

Procedures during visits 2 and 8 will be identical to those at visit 1, with the exception that additional blood samples will be collected during visits 5 and 8. An optional second skin biopsy will be collected prior to visit 7 to explore longitudinal changes in response to treatment.

##### Visit 9 (follow-up)

The procedure during the follow-up visit will be similar to that of the treatment phase, but will not include medication administration or biological sample collection.

### Patient adherence and study discontinuation

To improve adherence to the intervention protocol, all medication or placebo injections will be administered by the research assistant at the clinical study centre, which requires the attendance of patients. Similarly, all questionnaire data will be assessed prior to the medication administration on site.

Given the relatively low dosages of secukinumab in the reinforcement groups, topical treatments will be permitted as concomitant care in all three groups to enhance adherence and reflect real-life clinical care, as recommended by the S3 guideline for the treatment of psoriasis vulgaris. The study participation will be discontinued at any time at the patient’s request, if side effects are deemed intolerable by the patient and/or the treating physician or if the patient misses more than one visit. In such cases, the patient will be unblinded to the treatment allocation to allow appropriate subsequent medical care.

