### Missing data handling

All primary analyses will follow the intention-to-treat (ITT) principle, including all patients who received at least one active dose of the study medication and completed the acquisition phase (ie, attended visits 0–2). Patients meeting this criterion will be included in the analysis with all available data up to the point of dropout. By contrast, individuals who only attended the baseline assessment (visit 0) will be excluded from longitudinal modelling due to the absence of any post-baseline intervention exposure (ie, no medication or conditioned stimulus was administered). Missing data will be addressed using Full Information Maximum Likelihood (FIML) as the primary estimation approach. FIML leverages all available data points, including partially observed cases, by estimating model parameters based on the observed-data likelihood, without imputing missing values. This method is particularly suitable for complex mixed-effects models and preserves statistical power while minimising bias under the assumption of data missing at random (MAR).

Given the structured nature of data collection, where all assessments are completed on-site prior to medication administration, only a low proportion of missing data is expected. Reasons for missed visits (eg, illness, psychological burden) will be documented systematically through physician–patient contact and follow-up communication. In addition, a wide range of psychometric, demographic and clinical variables (eg, depression, anxiety, acute stress, treatment satisfaction) is collected, which increases the possibility that missingness is conditionally random (ie, MAR) and can be accounted for by observed data.

To empirically evaluate the MAR assumption, we will conduct logistic regression analyses to identify variables that significantly predict the occurrence of missing data. If no such variables are found, the originally specified analysis model will be estimated using FIML, without the inclusion of auxiliary covariates, thereby ensuring consistency with the pre-specified hypothesis structure.

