However, if significant predictors of missingness are identified, multiple imputation (MI) will be employed as a complementary strategy. In this case, auxiliary variables will be included in the imputation model only, while the analysis model will remain unchanged. This allows for the modelling of potential MAR mechanisms without introducing auxiliary covariates into the hypothesis-driven analysis, thereby preserving the interpretability of the predefined main and interaction effects.

To ensure sufficient information for reliable imputation, only participants with at least 7 out of 10 observed time points (ie, ≤30% missingness) will be included in the MI procedure. Participants with fewer than 7 observed time points will not be imputed but will remain in the FIML-based analyses in line with the ITT principle. In these cases, parameters will be estimated solely based on the likelihood of the available observations, without extrapolation.

A comparison between estimates obtained via FIML and MI will serve as a sensitivity analysis, evaluating the robustness of results under different plausible missing data assumptions, while maintaining a clear separation between hypothesis testing and missing data handling.

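### The primary set labelled ITT requires attendance at visits 0–2, so a treated patient who misses only visit 2 is followed to week 20 but left out of the primary analyses

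*Protocol article*

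**What the plan says.** Missing data handling opens with "All primary analyses will follow the intention-to-treat (ITT) principle" and then defines membership as "including all patients who received at least one active dose of the study medication and completed the acquisition phase (ie, attended visits 0–2"). The next exclusion it names is narrower: "individuals who only attended the baseline assessment (visit 0) will be excluded from longitudinal modelling", and the reason given is "due to the absence of any post-baseline intervention exposure". The same section selects FIML because it draws on every observed value, including those from incomplete cases. It adds that patients with fewer than 7 of 10 time points "will not be imputed but will remain in the FIML-based analyses in line with the ITT principle".

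Patient adherence and study discontinuation sets the retention rule. Among its grounds for ending participation, the one that concerns attendance is "or if the patient misses more than one visit". One missed visit is therefore tolerated.

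The acquisition phase is described under Dosing schedule and administration: "Patients in both reinforcement groups will initially receive weekly injections of 300 mg of secukinumab during an acquisition phase", at weeks 0–1. The TAU arm has no phase of that name, but it also receives 300 mg in those two weeks. The video and the drink start at visit 1, in the reinforcement arms only.

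**The concern.** An ITT set should not depend on what patients do after allocation. This one does: membership turns on attending visit 2, a week after treatment starts. A patient dosed at visit 1 who misses visit 2 and attends everything afterwards is retained, assessed to week 20 and then falls outside the stated set. The section's only reason for excluding anyone, lack of exposure, does not apply to that patient.

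Two things are at stake. First, endpoint data already collected are discarded, including the pre and post values on which Hypothesis 1 rests. Second, the filter operates once the arms have begun to differ. Reinforcement patients have seen the video and drunk the beverage at visit 1, and all patients have been told that the drink depends on group and that some groups receive lower doses. Attendance at visit 2 could therefore depend on arm, and selecting on it could disturb the randomised comparison behind the non-inferiority claim.

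**Working it through.** The plan states no figure to reproduce here; the check is one of logic.

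**Inputs**
- Visits: 0 (baseline), 1–8 (treatment), 9 (week 20), ten in all (Study schedule).
- Visit 2 is week 1. This is inferred by matching the eight treatment visits to the eight injection weeks 0, 1, 2, 3, 4, 8, 12 and 16. The biopsy section supports it, since it places visit 7 at 12 weeks.
- DLQI and PASI are taken at all ten visits; itch at visits 1–9 only (Outcomes).
- Retention rule: at most one visit missed.
- Primary-set rule: at least one active dose, and visits 0, 1 and 2 all attended.
- Assessments at each visit come before the injection.

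**The two rules applied to three patterns, each dosed at visit 1**

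| Attendance | Visits missed | Retained in trial | In primary set | DLQI/PASI | Itch |
|---|---|---|---|---|---|
| Misses only visit 2 | 1 | yes | no | 9 of 10 | 8 of 9 |
| Misses only one of visits 3–9 | 1 | yes | yes | 9 of 10 | 8 of 9 |
| Attends 0–2, then leaves | 7 | no | yes | 3 of 10 | 2 of 9 |

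The first two rows hold the same amount of data and differ only in which visit was missed. The third patient's last outcome is recorded at visit 2 before that day's injection, so it reflects a single injection; this patient is analysed. The first patient has follow-up to week 20 and is not. With 9 of 10 time points, the first patient would also clear the plan's own 7-of-10 threshold for imputation.

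**Comparison with the section's own reasons**
- Exposure: the patient was dosed at visit 1, so the ground given for excluding visit-0-only patients is absent.
- FIML: chosen so that incomplete cases contribute; here one missing visit removes the whole case.
- Sparse cases: kept expressly on ITT grounds, while a nearly complete case is not.
- Nothing elsewhere in the protocol brings the patient back.

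**How many patients**
The protocol gives no rate of missing visit 2. Assuming 1% to 5% of the 168 planned patients miss it and stay in:
- 168 × 0.01 = 1.68, about 2 patients
- 168 × 0.05 = 8.4, about 8 patients

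**The case against.** The strongest reply is that there is no conflict. The discontinuation rule decides who stays under study care and the other rule decides who is analysed; following someone who is outside a particular set is not inconsistent. That stands. A reader might infer that the two sections contradict each other, but they do not. The discontinuation rule only makes the weakness in the analysis set visible.

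Second, the exclusion sentence names only visit-0 patients, so the authors may have meant to keep the patient described here. That is possible, and it means settled intent to drop such patients cannot be claimed. The inclusion sentence as worded still leaves them out, so the text needs correcting on either reading.

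Third, the criterion selects on completed acquisition, not on the number of assessments. A patient with visits 0–2 had both full-dose pairings; one who missed visit 2 had one. This is a coherent rationale for a set that examines conditioning as delivered. It does not justify calling that set ITT or making it primary.

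Fourth, it is tempting to say that the condition means nothing in TAU, or that it breaks the randomised comparison. Both go too far. The condition is spelled out as attendance and applied alike to all arms, and every arm is scheduled to receive 300 mg at weeks 0 and 1, so doses have not diverged by visit 2. Only the video and drink differ. Differential absence is possible but not shown.

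Finally, the plan expects little missing data, and even 8 patients is half of the 16 added for dropout (168 − 152). No material loss of power is demonstrated.

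**Conclusion.** The point holds as a fault in how Missing data handling defines the primary set. A set described as ITT is filtered on attendance after randomisation. As written, it leaves out a treated, retained patient with 9 of 10 DLQI and PASI assessments and 8 of 9 itch assessments, for a reason the section does not give and against its own case for using all available data.

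The size is unknown: about 2 to 8 of 168 under an assumed 1–5%, with no attendance figure in the protocol to narrow that range. A reader might infer that the filter favours, or works against, a finding of non-inferiority. The protocol supports neither, because nothing shows which arm would miss visit 2 more often or how those patients would differ. The matter is worth correcting because the rule is explicit, the exclusion is avoidable and the change is small.

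**What to change.** Change the membership sentence in Missing data handling; the discontinuation rule can stay as it is. There are two acceptable forms:

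1. All randomised patients, analysed in their randomised arm with all available data. This matches the ITT label.
2. If never-treated patients are to be left out, all randomised patients who received the visit 1 injection, analysed in their randomised arm with all available data and labelled modified ITT. This is still an exclusion after randomisation, so it should not be called ITT.

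In either form, do not condition on attendance at visit 2. Keep the visits 0–2 set as a supportive analysis, where it answers the question about completed acquisition.

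The cost is a sentence or two of analysis wording, with no change to visits, treatment or data collection. The downside is small: a few reinforcement patients with one acquisition pairing instead of two enter the primary estimate. Patients who leave between visits 1 and 2 would also enter, but they contribute only values recorded before the first injection.
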